### 2.2.2 Safety

Comparisons are made with regard to the number of patients with treatment-related side effects among the three treatment arms. Abnormalities in laboratory tests (hemoglobin/hematocrit, liver function tests, calculated creatinine clearance), episodes of severe hypoglycemia, and incidence of side effects (e.g., gastrointestinal complaints, edema, weight gain) are tracked as outlined in detail in the chapter on safety and monitoring.

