#### 4.3 Masking

As noted above, during the run-in period, the patient is masked to the dose of metformin. Due to the established titration schedule for metformin and the need for dose adjustment according to side effects, staff are effectively unmasked to the dose of metformin.

After randomization, both patient and study staff are masked to medical management treatment arm.

After randomization, both patient and study staff are masked to HbA1c levels. Study staff are alerted if HbA1c  $\geq 8.0\%$ , or if HbA1c is between 6-8% with an increase between measurements  $\geq 0.8\%$ . Study staff are also alerted if HbA1c  $\leq 6\%$ .

A series of capsules containing all possible medication combinations is prepared and all types of capsules look identical. Participants take two capsules two times per day, at breakfast and at dinner. The table below presents all possible combinations of study medications.

| TODAY Study Medications                                                               |                    |                  |                    |                  |
|---------------------------------------------------------------------------------------|--------------------|------------------|--------------------|------------------|
| Total Daily Dose                                                                      | AM                 |                  | PM                 |                  |
|                                                                                       | Capsule 1          | Capsule 2        | Capsule 1          | Capsule 2        |
| • Run-in Period Only                                                                  |                    |                  |                    |                  |
| 500 mg metformin                                                                      | placebo            | placebo          | 500 mg metformin   | placebo          |
| • Run-in Period, or Metformin Only Treatment Arm, or Metformin Plus TLP Treatment Arm |                    |                  |                    |                  |
| 1000 mg metformin                                                                     | 500 mg metformin   | placebo          | 500 mg metformin   | placebo          |
| 1500 mg metformin                                                                     | 500 mg metformin   | placebo          | 500 mg metformin   | 500 mg metformin |

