## 6 Safety and Monitoring

### 6.1 Data Safety Monitoring Board (DSMB)

A Data Safety Monitoring Board consisting of appropriately qualified independent experts is appointed to provide review of data on patient safety. The purpose of the board is to assure independent review as to whether study patients are exposed to unreasonable risk because of study participation, and to monitor study progress and integrity. Board members are chosen by NIDDK in consultation with the study investigators, and a report format and reporting frequency are developed before the start of data collection. The study chair and the CoC provide periodic reports on adverse events to the committee, including summary tabulations and narrative summaries on individual events. The contents of reports are determined by the DSMB in its initial deliberations, including whether and when to perform interim efficacy analyses.

The purpose of safety reports is to present the Data Safety Monitoring Board with information regarding adverse events experienced by study patients as a result of undergoing the study procedures. Clinical centers report adverse events to the CoC in a timely fashion, including a narrative summary of the event as well as indication of the duration, perceived relationship to the study procedures, and resolution. The CoC summarizes and reports adverse events to the Data Safety Monitoring Board on a semi-annual basis unless severe or unexpected adverse events occur. These are reported promptly to the DSMB.

Following each DSMB meeting a summary of adverse events and DSMB recommendations is provided to the IRB of each participating clinical center and other institutional monitoring committees/boards as needed.

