#### 6.4.2 Definitions of Adverse Events

- *Adverse Event (AE)*: Any unfavorable and unintended change in the structure, function or chemistry of the body experienced by a study participant during the study regardless of the relationship of this change to administration of study intervention or participation in the study. Adverse events include symptoms and changes in laboratory data that are not specifically part of the primary or secondary outcomes of the trial. AEs are reported only at scheduled study visits unless they meet the criteria for being serious.
- *Serious Adverse Event (SAE)*: Events are divided into those that are serious (SAEs) and those that are not serious (AEs). The distinction between an SAE and an AE is a regulatory definition established by the FDA, not a clinical definition. The definition of SAE is not always related to clinical severity of the event. An AE is considered serious (SAE) when it satisfies any one of the following criteria:
  - a. The event results in an inpatient hospitalization (any overnight stay associated with an admission).
  - b. The event results in the prolongation of a hospital stay.
  - c. The event results in permanent or severe disability.
  - d. The event results in death.
  - e. A pregnancy results in a congenital anomaly.
  - f. The event results from an overdose (either accidental or experimental) of the study medication.
  - g. The event is life-threatening.
  - h. Treatment is required to prevent a serious event.
  - i. The patient experiences a bout of lactic acidosis.
  - j. An episode of severe hypoglycemia occurs.

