#### 6.4.5 Tracking of Adverse Events by the Study Group

- *Serious adverse events:* All SAEs are reported to the CoC within 24 hours. The CoC forwards all SAE reports to the chair of the Safety and Monitoring Committee for consideration. The committee chair assesses each event to determine if immediate action is required by the study group in response to the event. If the chair determines that immediate action should be considered, he/she consults with other members of the committee to recommend a course of action. In addition, any SAE that results in death or permanent or severe disability and any SAE judged by the local PI as PROBABLY or DEFINITELY related to study participation are discussed by the committee as soon as feasible. Any actions recommended are communicated to the study chair for consideration of study wide action. If the SAE is not deemed to warrant immediate study wide action, it is discussed at the next scheduled meeting of the Safety and Monitoring Committee.
- *Non-serious adverse events:* Non-serious adverse events (AEs) are tabulated by the Coordinating Center in the same format as is done for the Data and Safety Monitoring Board (DSMB). Summaries of the AEs, tabulated by clinic, are provided to the Safety and Monitoring Committee and discussed by them before each Steering Committee meeting. The committee reviews this summary during one of its regularly scheduled meetings and makes recommendations for action to the study group at the next Steering Committee meeting.
- *Meetings of the Safety and Monitoring Committee (SMC):* The SMC meets in person at the time of each study group meeting and by conference call at least every 4-6 weeks. During these meetings, the committee discusses all SAEs and, when available, the summary reports of the non-serious AEs. The committee considers whether changes in the protocol (monitoring, consent process, etc.) are indicated based on the occurrence, frequency, or severity of AEs and SAEs. The committee also evaluates whether there is any clustering of AEs by clinic. As deemed necessary, a member of the SMC

communicates with the local center PI to obtain additional information about SAEs and observed local trends in non-serious AEs. The SMC remains blinded to patient treatment group. If an SAE or pattern of AEs warrants unblinding, the issue is referred to the DSMB.

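### The between-arm safety comparison rests on an undefined treatment-related label, and site staff would apply that label with different knowledge of the drug in different arms

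*Protocol*

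**What the plan says.** **The comparison.** Section 2.2.2 states: "Comparisons are made with regard to the number of patients with treatment-related side effects among the three treatment arms". Its next sentence adds that laboratory abnormalities, episodes of severe hypoglycemia and "incidence of side effects (e.g., gastrointestinal complaints, edema, weight gain) are tracked", with no relatedness condition. Comparing the safety of the three arms is the first secondary aim in section 1.1.

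**Collection.** Section 6.4.2 defines an adverse event as an unfavorable change "regardless of the relationship of this change to administration of study intervention or participation in the study". Section 6.4.3 requires identical standard questions in all three arms.

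**Relatedness.** Section 6.1 has the centers report each event's "perceived relationship to the study procedures, and resolution". Section 6.4.5 refers to "any SAE judged by the local PI as PROBABLY or DEFINITELY related to study participation". Section 6.4.3, on non-serious events, mentions no relatedness rating.

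**Masking.** Section 4.3 says: "After randomization, both patient and study staff are masked to medical management treatment arm". Its capsule table groups the metformin-only capsules under "Run-in Period, or Metformin Only Treatment Arm, or Metformin Plus TLP Treatment Arm" and lists rosiglitazone only under the metformin plus rosiglitazone arm.

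**The concern.** A count of treatment-related events is the collected events passed through a causality judgment. If that judgment is made with different knowledge in different arms, the counts can differ although the true event rates do not.

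The lifestyle and metformin-alone arms take the same drug under the same rule (4.2.1.1). A drug-safety difference between them could therefore come from attribution alone. Lifestyle versus rosiglitazone could be distorted by the same route. Since this is the comparison that 2.2.2 states for the first secondary aim, its definition should not depend on who knew what.

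**Working it through.** The protocol gives no safety rate, attribution rate or safety power to reproduce. The check is a reading of the text, followed by an illustration.

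**1. What is compared and what is collected.** Section 2.2.2 compares a subset (treatment-related) of what 6.4.2 collects (all events). Comparing a subset of collected data is not a contradiction. The question is how the subset is chosen.

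**2. Who chooses it.** Two judgments are described, and both come from the sites: relationship to study procedures (6.1) and, for serious events only, relationship to study participation (6.4.5). Neither is worded as treatment-related. The Safety and Monitoring Committee is blinded to treatment group (6.4.5), but no blinded re-adjudication of relatedness is described.

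**3. What staff know, by arm.** Masking covers medical management. Lifestyle sessions are weekly in months 1-6, every two weeks in months 7-12, then monthly and later quarterly (4.4.4), so participation is visible. No capsule combination pairs the lifestyle program with rosiglitazone.

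| Arm | What staff who know of program attendance can infer |
|---|---|
| Metformin + lifestyle | No rosiglitazone |
| Metformin alone | Rosiglitazone cannot be ruled out |
| Metformin + rosiglitazone | Rosiglitazone cannot be ruled out |

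**4. Which events this can affect.**
- Edema and weight gain: sections 1.3.4 and 6.2.3 tie edema to rosiglitazone, and 1.3.4 also names weight gain. These are the main candidates.
- Anemia: weak, because 6.2.4 says either drug may cause it.
- Gastrointestinal complaints: weak, because they are mainly a metformin effect and metformin use is the same in all arms.
- Muscle soreness, injuries and hunger: 6.2.3 lists these as risks of the lifestyle program. If called treatment-related, they push the count the other way.

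**5. Illustration of size.** Inputs: n = 250 per arm (2.1). The true event rate r is equal in the metformin-alone and lifestyle arms, with r = 10% or 20% assumed. The shares called related, a1 (metformin alone) and a2 (lifestyle), are also assumed.

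Counted rates are p1 = r × a1 and p2 = r × a2.

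SE = √{[p1(1−p1) + p2(1−p2)] / 250}, and z = (p1 − p2) / SE.

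The chance of two-sided p<0.05 is Φ(z − 1.96) + Φ(−z − 1.96).

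For r = 20%, a1 = 50%, a2 = 25%: p1 = 0.10 and p2 = 0.05. SE = √[(0.0900 + 0.0475)/250] = 0.0235, z = 2.13, chance = 57%.

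| r | a1 v a2 | Counted rates | z | Chance of p<0.05 |
|---|---|---|---|---|
| 10% | 50% v 40% | 5.0% v 4.0% | 0.54 | 8% |
| 20% | 50% v 40% | 10% v 8% | 0.78 | 12% |
| 10% | 50% v 25% | 5.0% v 2.5% | 1.47 | 31% |
| 20% | 50% v 25% | 10% v 5% | 2.13 | 57% |

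Swapping a1 and a2 gives the same chances with the false signal against the lifestyle arm.

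**6. Without the filter.** Counting all events gives p1 = p2 = r. The expected difference is zero and the false-signal rate is the nominal 5%.

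**The case against.** The best counter-argument is that no section says a site rating feeds the 2.2.2 count. Section 6.1 concerns reports to the DSMB, 6.4.5 concerns which serious events the committee discusses promptly, and 6.4.3 has no rating for ordinary events. On this view treatment-related side effects means the known side-effect types of the study treatments, which the next sentence of 2.2.2 lists unfiltered. Many of these events also have objective criteria: numeric limits for anemia, transaminases and creatinine clearance, pitting above the ankle for clinically significant edema, and a set definition of severe hypoglycemia (6.2.4). Weight is measured at each visit.

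Much of this stands. The missing link to a rating is real, and objective criteria limit disagreement about whether an event occurred. They do not settle whether it was caused by treatment. The known-types reading is possible, but the protocol does not state it, and the literal words still impose a relatedness condition.

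It could also be said that choosing between all-cause and related tables belongs in the statistical analysis plan. Here the protocol itself states the comparison, so its wording can be judged.

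A reader might infer three stronger claims, none of which the documents support:
- **That 2.2.2 contradicts 6.4.2.** One governs comparison, the other collection.
- **That the filter undoes 6.4.3.** That section protects ascertainment, which stays identical across arms.
- **That the lifestyle arm will look safer than metformin alone.** Program-related events could reverse the direction, and no attribution rates are given.

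**Conclusion.** The point holds as a weakness in how the comparison is defined. On its literal wording, 2.2.2 compares arms on an undefined label. The only relatedness judgments described are made at sites, where knowledge of the drug differs between the lifestyle arm and the other two. This opens a route to bias, mainly for edema and weight gain; it does not demonstrate one.

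The 8% to 57% range rests wholly on assumed event rates and attribution shares, on equal true rates, and on an unadjusted two-sample test that the protocol does not specify for safety. The low end is close to the nominal 5%. The case for a change rests on an avoidable dependence on judgment in the first secondary aim, which a wording change removes.

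**What to change.** Reword 2.2.2 so that the between-arm comparison is the number of patients with each listed event (laboratory abnormalities, severe hypoglycemia, gastrointestinal complaints, edema, weight gain) regardless of judged relationship to treatment. Keep treatment-related counts as descriptive only.

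The cost is slightly more background events in the counts, which dilutes a true drug effect a little. No new data are needed, because 6.4.2 and 6.4.3 already collect events on this basis, and treatment and masking are unchanged.

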### 1.2 Overall Design and Study Interventions

The three treatment regimens are: (1) metformin alone, (2) metformin plus rosiglitazone, and (3) metformin plus an intensive lifestyle intervention called the TODAY Lifestyle Program (TLP). The study recruits patients over a three-year period and follows patients for a minimum of two years. Patients are randomized within two years of the diagnosis of T2DM. The primary outcome is time to treatment failure as defined below. The anticipated duration of the TODAY trial is seven years, including pre-trial planning and post-trial analysis and reporting.

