## 3 Recruitment, Screening, and Enrollment

### 3.1 Recruitment Goals and Strategies

The primary source of participants for the TODAY study is the active patient population of the study sites and their usual referral sources. Supplemental strategies for increasing referrals (such as presentations to local physician groups) are also utilized. Site-specific recruitment strategies are developed by each local study team. The period of recruitment is anticipated to last four years.

The TODAY sites were chosen partially based on the ethnic/racial composition of their patients with T2DM. It is estimated that the ethnic/racial distribution of enrolled participants will be 33% African American, 31% Hispanic (largely Mexican American), 12% Native American, 20% non-Hispanic White, and 4% other (largely Asian American). Study sites will develop targeted strategies for maximizing the recruitment of the particular racial and ethnic groups seen in clinic.

Recruitment efforts are integrated into and supported by other TODAY activities, including national and local public relations efforts, on-going development and adaptation of recruitment and advertising materials, and presentations at local and national meetings. Recruitment of current patients as well as community-based recruitment will begin in parallel from the start of the enrollment period.

Recruitment progress is monitored regularly by the coordinating center and the Recruitment and Retention Committee. Limited, anonymous data are collected on individuals who refuse to participate in order to tailor the recruitment process. Assistance is offered to clinical centers struggling with recruitment efforts.

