## 5.3 Participant Retention Program

Retention refers to efforts to prevent participant dropout or withdrawal from the study. It is critically important to successfully engage and retain participation over the course of the trial. For purposes of sample size estimation, investigators have predicted withdrawal rates of 10% over each 6 month follow-up period. However, lower rates of attrition are desirable.

Challenges to retention include:

- *Burden* (e.g., the imposition caused by study procedures, frequent scheduling of procedures and study-related visits, the requirement for record keeping, the necessity of frequent glucose monitoring, the interference of study activities with other things the participant would like to do)
- *Logistics* (e.g., travel required for study participation, care of non-participating children while the parent is at a study visit, difficulty with dietary requirements such as limited access to fresh fruits and vegetables)

- *Environment* (e.g., lack of supportive individuals and institutions, deficits due to locale such as the lack of a grocery store or a safe place to be active)
- *Education* (e.g., low literacy, familial misinformation about diabetes, sociocultural mismatch between family and educator, language barriers)
- *Distrust* (e.g., the perception by the participant and/or family of being used as a 'guinea pig,' general suspicion of medical personnel or organizations, wariness of people of different ethnicity or race).

Specific strategies to systematically address each of these areas are developed. Activities at both the national and local level are utilized and coordinated to maximize retention and minimize attrition. For example, in response to the perception that "the study team is more interested in the study than the individual," the TODAY study maintains a database of ideas about positive approaches to participants. At the local level, study staff make a major effort to personalize the study (mailing out personal notes, birthday cards, etc). Individual sites develop strategies to enhance retention specific to locale (i.e., different strategies may be required in Oklahoma working with rural Native Americans as compared to working with urban African Americans in Philadelphia).

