# 8 Statistical Considerations

## 8.1 Sample Size

The primary outcome for the TODAY study is time to treatment failure, defined as persistently elevated HbA1c levels ( $\geq 8.0\%$  for 6 months) or the inability to be weaned safely from temporary use of insulin therapy. No published data exist that allow estimation of the rate of occurrence. From unpublished data collected in the participating clinical centers, it is estimated that between 10-20% of children will have an HbA1c above the threshold by the end of each 6 month period, beginning at the end of the first year. The following assumptions were used to determine the sample size goal for TODAY:

- Primary outcome is time to failure as defined above.
- Eligible patients are randomized evenly to one of three treatment arms and followed for an additional two years following close of randomization.
- Rate of treatment failure within treatment group is constant over time.
- Treatment failure in the reference group (metformin alone) is at least 10% per six-month period, beginning at the first annual visit.
- There is a reduction of at least 40-50% in the treatment failure rate in one of the more intensively treated groups.
- Ten percent of patients are lost to drop-out during each 6 month period.
- The type I error rate ( $\alpha$ ) is 0.05 (two-sided) with a Bonferroni adjustment [Miller 1981] for three pair-wise comparisons of the three treatment groups.

Given these assumptions, if 10% of the metformin group has an HbA1c above the threshold, 250 participants per arm provides at least 90% power to detect a 50% reduction in the treatment failure rates in at least one combination therapy group (i.e., 5% with HbA1c above threshold during a six-month period). If 20% of the metformin group has an HbA1c above the threshold, 250 participants per treatment arm provides at least 90% power to detect a 40% reduction in hazard rates in at least one of the combination therapy groups (i.e., 12% failing during a six-month period). Therefore, 250 participants per group are recruited.

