## 8.2 Statistical Analysis

The principal analyses of primary and secondary outcomes employ the "intent-to-treat" approach [Peduzzi et al. 1993]. The intent-to-treat analyses include all randomized patients with all patients included in their randomly assigned treatment group; treatment group assignment is not altered based on the patient's adherence to the assigned treatment regimen. All statistical tests are two-sided with the overall significance level of the primary outcome  $\alpha$

$\alpha = 0.05$ . However, b

TODAY, the significance levels used in the interim and final analyses of the primary outcome are adjusted to account for the multiplicity of interim analyses.

- *Baseline characteristics:* Comparison of the baseline characteristics among the three treatment groups uses standard nonparametric statistical techniques, such as Fisher's exact test for categorical data and the Kruskal-Wallis test for ordinal or continuous data.
- *Primary outcome:* The principal analysis of TODAY is an analysis of the time to treatment failure. Turnbull's [1976] algorithm is used to calculate and compare Peto's [1973] nonparametric estimates of the interval-censored survival curves for each treatment group. For the primary outcome analysis, patients are considered "administratively censored" if they complete the full duration of TODAY without having failed. Patients who prematurely discontinue their follow-up visits without having reached study endpoint are "censored" as of their last follow-up visit. Failure is considered to have occurred during the interval between the last HbA1c value  $< 8\%$  and the first HbA1c value used to classify the participant as a treatment failure.
- *Secondary outcomes:* Secondary time to "event" outcomes (e.g., cardiovascular risk factors, microvascular outcomes) are analyzed using the same life-table methods described above for the primary outcome. A proportional-hazards regression model is used to evaluate potential covariates that may modify the primary and secondary time to

event outcomes (e.g., risk population defined by race/ethnicity, age, clinical site). Graphical procedures are used to assess the proportionality assumption. If the proportionality assumption is found to be unreasonable, then other models such as the accelerated failure time model [Wei 1992] or the proportional odds model [McCullagh 1980] are used to evaluate the covariates.

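### The stated safety comparison counts affected patients without regard to observed time, so it is fair only if the arms lose patients at the same rate

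*Protocol*

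**What the plan says.** Comparing safety is the first secondary aim in Section 1.1. Section 2.2.2 states the comparison: "Comparisons are made with regard to the number of patients with treatment-related side effects among the three treatment arms". The same section adds that laboratory abnormalities, severe hypoglycemia and "incidence of side effects (e.g., gastrointestinal complaints, edema, weight gain) are tracked", and refers to the safety chapter for detail. Chapter 6 covers monitoring and reporting but gives no method for comparing arms and no person-time denominator.

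Follow-up is unequal by design. Section 1.2 says "The study recruits patients over a three-year period and follows patients for a minimum of two years", and Section 8.1 has patients "followed for an additional two years following close of randomization". Section 3.1 gives a different recruitment length: "The period of recruitment is anticipated to last four years". On loss, Section 5.3 says "investigators have predicted withdrawal rates of 10% over each 6 month follow-up period"; Section 8.1 uses the same rate, with no distinction by arm.

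In Section 8.2, secondary time-to-event outcomes "are analyzed using the same life-table methods described above for the primary outcome". The examples given there are cardiovascular risk factors and microvascular outcomes. Side effects are neither named nor excluded.

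**The concern.** A count of patients ever affected depends on two things: the hazard of the side effect, and how long each patient was watched. When arms differ in the second, the count no longer isolates the first. An arm that sheds patients faster has less time in which to record a first event, and so looks safer at the same hazard. A true excess in that arm can be masked, or an apparent advantage can arise where none exists.

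Unequal loss is possible here. Section 5.3 lists participant burden among the challenges to retention, including "the imposition caused by study procedures, frequent scheduling of procedures and study-related visits". Under Section 4.4.4 the lifestyle arm alone has weekly sessions for six months, bi-weekly sessions to month 12, monthly sessions to month 24 and quarterly sessions after that. The direction is uncertain, since extra contact might equally improve retention. A count is distorted either way.

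**Working it through.** **Inputs from the protocol.** 250 per arm (Section 2.1); entry over 3 years with 2 more years after randomization closes (Sections 1.2 and 8.1), so follow-up time T is spread over 2 to 5 years; drop-out of 10% per 6 months (Sections 5.3 and 8.1).

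**Assumptions, because the protocol gives no figure.** Uniform entry, a constant side-effect hazard h, exponential drop-out, the unequal drop-out rates, and a two-sided two-proportion z-test at 0.05. The protocol names no test for side effects.

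**Check of the shared inputs.** The protocol states no figure for the safety comparison, but its primary-outcome power uses the same accrual and drop-out. With failures counted from the 6-month period that ends at the first annual visit, two arms yield 122.4 events (10% v 5% failing per 6 months, hazard ratio 0.5) or 218.3 events (20% v 12%, hazard ratio 0.6). By the Freedman form, with alpha 0.05/3 and z = 2.394:
- √122.4 × (0.5/1.5) − 2.394 = 1.29, power 90.2%
- √218.3 × (0.4/1.6) − 2.394 = 1.30, power 90.3%

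The stated power of at least 90% is reproduced. If risk is counted only from month 12, it is 82–85%.

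**Observed time.** At 10% loss per 6 months, 0.9⁴ = 66% remain at 2 years and 0.9¹⁰ = 35% at 5 years. About 49% reach close-out, and mean follow-up is 2.4 years.

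**Expected proportion affected.** With 6-month drop-out q, d = −2 ln(1 − q) per year and k = h + d. Averaging h/k × (1 − e^(−kT)) over T from 2 to 5 years gives

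p = (h/k) × [1 − (e^(−2k) − e^(−5k)) / (3k)]

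With h = 0.10 in both arms:
- q = 10%: d = 0.2107, k = 0.3107, p = 0.3219 × [1 − (0.5372 − 0.2115)/0.9322] = 20.9%
- q = 15%: d = 0.3250, k = 0.4250, p = 0.2353 × [1 − (0.4274 − 0.1194)/1.2751] = 17.8%

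The ratio is 0.178/0.209 = 0.85. The pooled standard error is √(2 × 0.194 × 0.806/250) = 0.0354, so the expected z is about 0.031/0.0354 = 0.87, and the chance of a nominally significant difference is 0.14 instead of 0.05.

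**Range, 3-year accrual, same hazard in both arms:**

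| Hazard per year | Drop-out per 6 months | Ratio of proportions | Chance of p < 0.05 |
|---|---|---|---|
| 0.10 | 10% v 10% | 1.00 | 0.05 |
| 0.10 | 10% v 12% | 0.94 | 0.065 |
| 0.10 | 8% v 12% | 0.88 | 0.12 |
| 0.10 | 10% v 15% | 0.85 | 0.14 |
| 0.20 | 10% v 15% | 0.86 | 0.22 |

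With 4-year accrual, 10% v 15% gives ratios of 0.84–0.85 and a chance of 0.17–0.26.

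**Masking of a true excess.** With h = 0.12 (20% higher) in the arm with 15% drop-out, the same formula gives 20.85% against 20.94% in the arm with 10% drop-out, so the excess disappears.

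**Early-onset effects.** If a 20% cumulative risk falls entirely in the first 6 months, 10% v 15% drop-out gives a ratio of 0.97 and a chance of 0.052. If it falls in the first 12 months, they are 0.95 and 0.058.

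**With time taken into account.** Mean time at risk to first event is p/h: 2.09 years at 10% drop-out and 1.78 at 15%. Dividing each proportion by its own time gives 10 first events per 100 patient-years in both arms, a ratio of 1.00.

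**The case against.** The strongest reply is that Section 2.2.2 describes an outcome and not a test, and that a statistical analysis plan not shown here may add exposure-adjusted rates. The section also uses the word incidence, and the examples in Section 8.2 are not exhaustive, so its life-table methods could be read to cover side effects. This stands in part: the text is open to that reading. But the sentence in 2.2.2 does name a measure for the comparison, the number of patients, and an analysis plan that follows it inherits the count. The point concerns what is stated, not what is absent.

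A reader might infer that variable follow-up alone biases the comparison. It does not: 1:1:1 allocation in permuted blocks within center (Section 3.3) balances planned follow-up. Bias needs unequal loss, and the protocol assumes a single rate and predicts no difference.

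A reader might also infer that burden is the main threat to retention and that the lifestyle arm will therefore look safer. Section 5.3 gives an unranked list. The session load bears only on comparisons with the lifestyle arm; the two drug-only arms share a visit schedule and are masked with identical capsules (Section 4.3).

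Finally, the constant hazard is a chosen case. Section 6.2.4 says gastrointestinal symptoms tend to come early in treatment, and for such effects the distortion is slight. That objection stands and limits the size of the point.

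**Conclusion.** The point holds as a weakness of the stated measure. Section 2.2.2 compares numbers of affected patients and makes no allowance for observed time, in a trial with planned follow-up of 2 to 5 or 6 years and heavy expected loss. With equal loss the between-arm comparison is fair, although the crude proportion mixes different exposures and is not a risk at any stated time.

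If loss differs, the arm losing more looks safer. The ratio is 0.85 at 10% v 15% drop-out under a constant hazard, 0.94 with an error rate near nominal at 10% v 12%, and 0.95–0.97 at 10% v 15% when the effect arises in the first year. The hazards and the unequal drop-out rates are assumptions. The documents do not support saying that the safety comparison is biased, or in which arm's favour it would be.

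**What to change.** In Sections 2.2.2 and 8.2, state that each side effect is compared between arms by time from randomization to the first visit at which it is recorded, using the interval-censored life-table method already named in 8.2, with censoring at last follow-up. Report incidence per patient-year by arm, and keep numbers of patients as description. Reconcile the three-year and four-year recruitment statements in Sections 1.2 and 3.1, since they set the range of follow-up.

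Visit-based timing is the safe choice: Sections 6.4.2 and 6.4.3 have non-serious events recorded at scheduled visits, and the protocol does not say that onset dates are collected.

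The cost is a sentence or two and a little more analysis, with no new visits or data. The method does assume that leaving is unrelated to harm, which is doubtful if side effects prompt withdrawal. Drop-out and reasons for leaving, which Section 5.3 already tries to collect, should therefore be shown by arm beside the rates.
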